# Intervention

The treatment consists of two daily doses of 109 mg of ferrous sulfate in the form of pills with 40 mg of elemental iron (Hematofer®, Prati Donaduzzi & Cia LTDA). Three blisters with 20 pills are given at the enrollment ( $C_0$ ) and at the two monthly revaluations ( $C_1$ ,  $C_2$ ). The pregnant women are oriented at each consultation to ingest the medication with a glass of drinking water, 30 - minutes before a meal, and to preserve the non-consumed pills in the blisters. The safety profile for the use of ferrous sulfate at pregnancy is satisfactory; there were no reports of fetal damage or severe maternal adverse events [19,20]. The dose of 80 mg/daily of elemental iron was adopted due to the set of evidences not found any additional efficacy with higher daily doses [14,19].

[figure not shown]

**Figure 1** Flowchart of the participant enrolled in the AMA study until August 2012.

### Follow-up and withdrawal criteria

The prescribed treatment provides a follow-up period of 90 days. The follow-up is stopped before this period in case of evolution to high-risk pregnancy, genital bleeding, childbirth delivery, drop out of treatment, use of another type of iron supplement, drug intolerance, cure or aggravation of anemia. The participants are evaluated monthly ( $C_1$ ,  $C_2$ ,  $C_3$ ), and information about gastrointestinal symptoms and therapeutic compliance is collected by the standardized form, such a venous blood sample to obtain Hb is prompted. Pregnant women who present drug intolerance, severe anemia ( $Hb < 7.0$  g/dL) or Hb values drop more than 1.0 g/dL during the follow-up are referred to an individualized conduct. Those who present  $Hb > 11.0$  g/dL before 90 days of the overall follow-up will begin to use supplemental doses of oral iron (40 mg/daily).

### Studied tests (predictive variables)

The initial values of the erythrocyte indices and serum ferritin will be tested as predictors of presence of the functional iron deficiency at the following cutoff points suggested by WHO and Centers for Disease Control and Prevention (CDC) on pregnant or childbearing age women (when there is no specific report for pregnant women): red blood cells count  $< 3.8 \times 10^{12}$  cells/L;  $Hb < 10.5$  g/dL (suggested for the 2nd trimester of pregnancy); haematocrit  $< 32.0\%$  (suggested for the 2nd trimester of pregnancy); mean corpuscular volume (MCV)  $< 81.0$  fL; mean corpuscular haemoglobin (MCH)  $< 26.0$  pg; mean corpuscular haemoglobin concentration (MCHC)  $< 32.0$  g/dL; red blood cells distribution width (RDW)  $> 14.0\%$ ; reticulocyte count  $< 1.0\%$ ; serum ferritin  $< 12.0$  ng/mL [1,21,22].

### Gold-standard test (outcome variable)

The final diagnosis of iron deficiency will be set individually on the basis of the presence (case) or absence (non-case) of the 'responsiveness to therapeutic test with oral iron', starting from assumptions that, in the case of iron deficiency in pregnancy, a functional definition would be more appropriate [37] and the haematologic response to the treatment is considered as a reliable indicator of functional iron need [1]. This is one of the alternative approaches in the definition of the gold-standard which is based on the follow up of the clinical course during a suitable predefined period under a therapeutic intervention [36].

To measure this outcome, the physiological variability of Hb throughout the pregnancy was taken into consideration, because it distorts the interpretation of longitudinal trends of Hb absolute values [33]. Thus, on the rationale basis developed by Beaton and McCabe in 1999, the pre and post treatment Hb values of each

pregnant woman will be adjusted to the gestational week through the Z-score methodology [33]. This methodology quantifies the difference (in standard deviation units-SD) between an observed Hb value and the gestational week's reference mean from a reference distribution curve [33]. Due to the lack of a Brazilian reference curve will be used the curve reported from iron-supplemented healthy women from Europe and North-America which was employed by Beaton and McCabe [21,22,33]. The individual calculation of the Z-score is carried out according to the following mathematical formula:

$$HbZ - score = \frac{(Hb \text{ value observed} - \text{mean of Hb expected})}{SD \text{ of the reference population}}$$

It was determined as a final diagnosis of functional iron deficiency the partial therapeutic responsiveness by increase of at least 0.55 Hb Z-score after a minimum of 4 weeks treatment and an intake of at least 1200 mg of elemental iron as a total dose, based on the following assumptions:

- An increase of 1 g/dL on the Hb after 30 to 60 days of oral iron therapy is a reliable indicator of iron deficiency in individuals or populations [1].
- The haematological improvement depends on the total dose of iron intake considering that the dose of 1200 mg of elemental iron is responsible for most of the effect on the Hb values [14].
- The standard deviation of the Hb distribution in populations of pregnant women is 0.9 g/dL, independently of gestational age [33].
- By mathematics definition, 1 Z-score corresponds to 1 SD, that is, equal to 0.9 g/dL of Hb at pregnancy. Therefore, the difference of 0.55 SD between the post and pre-treatment Hb Z-scores represents a relative increase of 0.5 g/dL ( $0.55 \times 0.9$  g/dL) in the Hb status of a pregnant woman.

### Confounding variables (secondary outcomes)

Treatment compliance and adverse effects are being evaluated every 30 days and recorded in the pregnant women's individual form with a goal to reduce losses and ensure the intake of the effective total dose of iron with minimal symptomatic discomfort for the pregnant women. Women who do not achieve the minimum adherence (intake of 30 pills = 1200 mg of elemental iron) will not be evaluated for the 'responsiveness to therapeutic test with oral iron'. The frequency of the good adherence to the treatment will be reported as an intake at least 75% of the prescribed monthly pills, according to pregnant women's information and pill counting. This percentage was determined on the basis of the proportion

of the monthly treatment prescribed that corresponds to the total monthly dose of 1800 mg of elemental iron, which is considered responsible for almost the entire effect in Hb levels according to Ekström *et al.* (2002) [14].

According to pregnant women's information the presence of the adverse effects was defined as the appearance of the following symptoms after the beginning of the intervention: abdominal pain/abdominal cramps, diarrhea (increasing number of evacuations or reduction of the stools consistency), constipation (reducing number of evacuations or hardening of stools), nausea, vomiting and heartburn (epigastric burning or heartburn) [38]. The women who developed symptoms related to the medication are orientated case by case to ingest the pills along with the meals or temporarily reduce the dosage for a pill a day.

The following *co-variables* are being collected for the sample characterization: age, city of residence, education level, socioeconomic class (economic classification criteria Brazil 2010) [39], marital status; anthropometric classification by the body mass index (Atalah *et al.* standard) [40], number of pregnancies, births or miscarriages and last inter-gestational interval. The gestational age is being defined as complete weeks from the date of the last menstrual period and confirmed by ultrasound estimation. In pregnant women who do not remember their last menstrual period, the gestational age will be based solely on the ultrasound examination.

## Statistical issues

### Sample size

The sample size (43 cases and 97 non-cases) was calculated to estimate 90% of sensitivity and 80% of specificity, with relative error of 10% and the power of 95%. Considering cure rates of 50% and 30% of losses or poor adherence to treatment [38,41], 278 anemic pregnant women should be recruited.

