## Abstract

**Background:** Pregnancy anemia remains as a public health problem, since the official reports in the 70's. To guide the treatment of iron-deficiency anemia in pregnancy, the haemoglobin concentration is the most used test in spite of its low accuracy, and serum ferritin is the most reliable test, although its cutoff point remains an issue.

**Methods/design:** The aim of this protocol is to verify the accuracy of erythrocyte indices and serum ferritin (studied tests) for the diagnosis of functional iron-deficiency in pregnancy using the iron-therapy responsiveness as the gold-standard. This is an ongoing phase III accuracy study initiated in August 2011 and to be concluded in April 2013. The subjects are anemic pregnant women (haemoglobin concentration < 11.0 g/dL) attended at a low-risk prenatal care center in the Northeast of Brazil. The sample size ( $n$  278) was calculated to estimate sensitivity of 90% and 80% of specificity with relative error of 10% and power of 95%. This study has a prospective design with a before-after intervention of 80 mg of daily oral iron during 90 days and will be analyzed as a delayed-type cross-sectional study. Women at the second trimester of pregnancy are being evaluated with clinical and laboratorial examinations at the enrollment and monthly. The 'responsiveness to therapeutic test with oral iron' (gold-standard) was defined to an increase of at least 0.55 Z-score in haemoglobin after 4 weeks of treatment and a total dose of 1200 mg of iron. At the study conclusion, sensitivities, specificities, predictive values, likelihood ratios and areas under the ROC (Receiver Operating Characteristic) curves of serum ferritin and erythrocyte indices (red blood cell count, haematocrit, haemoglobin concentration, mean corpuscular volume, mean corpuscular haemoglobin, mean corpuscular haemoglobin concentration, red blood cell distribution width, reticulocyte count) will be tested. The compliance and adverse effects are considered confounding variables, since they are the main obstacles for the iron-therapy responsiveness.

**Discussion:** This study protocol shows a new approach on iron-deficiency anemia in pregnancy from a functional point of view that could bring some insights about the diagnostic misclassifications arising from the dynamic physiologic changes during the gestational cycle.

**Trial registration:** WHO International Clinical Trials Registry Platform U1111-1123-2605.

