The haemoglobin concentration (Hb) has been considered as a *proxy* of iron deficiency and widely recommended as a criterion for the indication of iron-therapy in pregnant women, particularly in location with few resources [1]. The Hb cutoff point of 11.0 g/dL for pregnancy was defined from North American and European reference populations by the Gaussian paradigm: less than 2 standard deviations below the mean reference [1,21,22]. This is a theoretical statistic definition that assumes prevalence of 5% for all disorders and might not be suitable for all epidemiologic or clinical settings [23]. Indeed, the 70's guideline of the World Health Organization (WHO) considered that the Hb cutoff points defined from population distributions could be an oversimplification [10]; and some studies have observing that Hb and other erythrocyte indices present low correlation with the body iron reserves in pregnant women (sensitivity and specificity

around 60%) [24-29]. Thus, could be considered that diagnostic misclassifications of iron-deficiency anemia may be another limiting factor of the iron-therapy responsiveness in this life cycle phase.

In fact, the cross-sectional and longitudinal assessment of the haematological profile during pregnancy is troublesome due to increased iron requirements beside the haemodilution, a physiological phenomenon in which occur an increase of 50% in the plasma volume *versus* 30% in the erythrocyte mass [1,21]. This phenomenon is responsible for the U-shaped curve that Hb and haematocrit levels develop in pregnant women with nadir between the 24th and 28th weeks of pregnancy [24,30-32], which explains the "physiological anemia" in which the erythrocyte mass remains normal in relation to the effective body weight [1,7]. Based on this rationale, Beaton and McCabe (1999) developed the Hb Z-score methodology to correct its values according to the mean expected for the gestational week [33]. An alternative to a more accurate diagnosis of iron deficiency would be the dosage of biomarkers of iron metabolism, however, these are also influenced by gestational physiology and many have not been standardized to be used at pregnancy [1,34]. The serum ferritin remains as the biomarker that best correlates with the iron content in the bone marrow of pregnant women [24-27], but there is no consensus as to its cut-off point [1,34].

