### Operational and data analysis

The data are being released with dual input and processed in the EPIINFO3.4.2 program. The analytical design is as a delayed-type cross-sectional study, where at the end of the follow-up, the measured tests at time-zero (predictive variables) will be compared with the final diagnosis of the target-disease (outcome variable) to determine estimates of accuracy [36]. Thus, at the end, the proportions and its confidence intervals will be calculated for sensitivity, specificity, accuracy, predictive values, likelihood ratios and areas under the ROC curves of each erythrocyte index and serum ferritin against the presence or absence of the 'responsiveness to therapeutic test with oral iron'. The significance level adopted will be 5%. The estimates will be made according to the 3 × 3 table for the results distribution from diagnostic accuracy phase III studies, which have cells to report unconcluded

results (lost, not performed or indeterminate) of the gold standard and the studied tests [23]. This table enables to report the results unknown that could bias the measurement of accuracy at a clinical practice setting (Table 1).

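### The stated 95% power is a 95% confidence level, and the 10% relative error is met only by tests at least as accurate as the plan assumed

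*Protocol*

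**What the plan says.** The Sample size section under Statistical issues reads "The sample size (43 cases and 97 non-cases) was calculated" and gives the basis as "to estimate 90% of sensitivity and 80% of specificity, with relative error of 10% and the power of 95" per cent. It then allows for a 50% cure rate and for 30% lost or poorly adherent, and arrives at 278 women to recruit. The Abstract says the same of the total: the sample "was calculated to estimate sensitivity of 90% and 80% of specificity with relative error of 10% and power of 95" per cent.

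Two other places bear on this. The Background reports that in earlier studies haemoglobin and the other erythrocyte indices agreed poorly with body iron reserves, with sensitivity and specificity "around 60%) [24-29]. Thus, could be considered that diagnostic misclassifications of iron-deficiency anemia may be another limiting factor". The hypothesis at the end of the Background is that these indices predict poorly and that serum ferritin does better; it attaches no figure to either. The section on Operational and data analysis plans estimation: "the proportions and its confidence intervals will be calculated for sensitivity, specificity, accuracy, predictive values, likelihood ratios and areas under the ROC curves", for each test, with a 5% significance level.

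**The concern.** Power is the probability of rejecting a stated null value when a stated alternative is true. The sample size statement gives neither. It speaks of estimating two proportions to within a relative error, which is the language of precision. If the 95% is only the confidence level of an interval, readers of the Abstract will credit the study with a property it does not have.

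The second issue is scope. The only precision the protocol states is for a test with 90% sensitivity and 80% specificity. Eight of the nine tests listed under Studied tests are erythrocyte indices, which the hypothesis expects to do poorly. For a fixed number of women, relative error grows as the true proportion falls. Estimates for those tests could be read as precise to within 10% when they are not.

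**Working it through.** **Inputs.** From the Sample size section: sensitivity 0.90, specificity 0.80, relative error 0.10, 43 cases, 97 non-cases, cure rate 50%, losses 30%, 278 recruited. From the Background: about 0.60 for the indices.

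**Step 1: reproduce the plan's figures.** A two-sided 95% interval for a proportion p with half-width 0.10p needs

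n = 1.96² × (1 − p) / (p × 0.10²)

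- p = 0.90: 3.8416 × 0.10 / (0.90 × 0.01) = 42.7, rounded up to 43.
- p = 0.80: 3.8416 × 0.20 / (0.80 × 0.01) = 96.04, rounded up to 97.
- Recruitment: 97 / 0.50 / (1 − 0.30) = 277.1, rounded up to 278.

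All three match, and no power term enters.

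**Step 2: check that other readings do not match.** A one-sided 95% limit gives 31 and 68. An absolute error of 10 points gives 35 and 62. Adding a real 95% power term to the same formula (1.96 + 1.645 in place of 1.96) gives 145 and 325. None of these yields 43 and 97, so the 95% entered only as the confidence multiplier.

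**Step 3: where the 10% holds.** Rearranged, the relative error is 1.96 × √[(1 − p)/(p × n)], which falls as p rises.

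- Sensitivity with 43 cases: 9.96% at p = 0.90. The target is met at 90% or above.
- Specificity with 97 non-cases: 9.95% at p = 0.80. The target is met at 80% or above.
- Expected cases: 278 × 0.70 × 0.50 = 97.3, taking the 50% cure rate as the share of cases, as the plan's own arithmetic does. With about 97 cases, sensitivity down to about 80% also meets 10%.

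**Step 4: precision at lower accuracy.** The half-width is 1.96 × √[p(1 − p)/n].

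| True value | Half-width, n = 97 | Relative | Half-width, n = 43 | Relative | n per group for 10% |
|---|---|---|---|---|---|
| 0.70 | 9.1 points | 13% | 13.7 points | 20% | 165 |
| 0.60 | 9.7 points | 16% | 14.6 points | 24% | 257 |
| 0.50 | 10.0 points | 20% | 14.9 points | 30% | 385 |

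For example, at 0.60 with 97 women: 1.96 × √(0.24/97) = 0.097, and 0.097/0.60 = 16%. The size needed for 10% is 3.8416 × 0.40 / (0.60 × 0.01) = 256.1, rounded up to 257. The n = 43 columns apply to sensitivity only, and only if no more than the minimum number of cases accrues.

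**The case against.** The best defence is that the sample size is right and one word is wrong. All three figures follow from the stated inputs, the sentence itself speaks of estimating with a relative error, and the analysis section plans intervals. Correcting the label changes no patient and no analysis. That stands, but it does not excuse the label: the wrong property is claimed twice, once in the Abstract.

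The defence on precision also has force. At the plan's own assumptions about 97 cases are expected, so 43 is a floor and the 24% figure is a worst case. In absolute terms the loss with 97 per group is modest: 9.7 points at 60% against 8.0 points at 80%. Relative error looks worse partly because its denominator is smaller.

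Four stronger readings are tempting, and the protocol does not support them.

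- *The study is underpowered and must be enlarged.* Any power figure needs a null value, and the protocol names none. The 257 per group shows what 10% relative error would need at 60%; the plan did not promise that.
- *The 10% holds only for a test at exactly 90% and 80%.* It holds for any test at least that accurate.
- *The protocol expects eight of nine tests to perform at 60%.* The Background figure comes from studies against body iron reserves, whereas here the reference standard is response to oral iron. The hypothesis gives no number.
- *The comparison of ferritin with the indices is planned wrongly.* The protocol gives no inputs from which to size it. The choice of a paired method is something a statistical analysis plan may settle.

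**Conclusion.** The point holds on two counts of unequal weight.

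First, the 95% power in the Sample size section and the Abstract is a mislabelled 95% confidence level. This rests on exact reproduction of 43, 97 and 278 and on the absence of any null value or difference, so it is certain for practical purposes. The design does not have 95% power.

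Second, the 10% relative error is conditional. It needs specificity of at least 80% with 97 non-cases, and sensitivity of at least 90% with 43 cases or at least about 80% with the roughly 97 cases expected. Near 60% the delivered relative error is about 16% with 97 per group and 24% at the 43-case minimum. Across true values of 50% to 70% with 97 per group it runs from 20% to 13%, so the target is missed throughout. Applying such values to this reference standard is an assumption. The expected 97 cases also depends on the plan's 50% and 30% rates being borne out.

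**What to change.** In the Sample size section and the Abstract, replace the 95% power with a 95% confidence level, and say that it is two-sided.

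Add one sentence stating that the 10% relative error applies to tests with at least the assumed accuracy. Then give the expected precision for accuracy of about 50% to 70%: half-widths of about 10.0 to 9.1 points with 97 women per group, and 14.9 to 13.7 points for sensitivity if only 43 cases accrue. Mark that range as an assumption.

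The cost is a few lines of text. No more patients and no new analysis are needed. The only downside is that the stated figures become less favourable.

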### Operational and data analysis

The data are being released with dual input and processed in the EPIINFO3.4.2 program. The analytical design is as a delayed-type cross-sectional study, where at the end of the follow-up, the measured tests at time-zero (predictive variables) will be compared with the final diagnosis of the target-disease (outcome variable) to determine estimates of accuracy [36]. Thus, at the end, the proportions and its confidence intervals will be calculated for sensitivity, specificity, accuracy, predictive values, likelihood ratios and areas under the ROC curves of each erythrocyte index and serum ferritin against the presence or absence of the 'responsiveness to therapeutic test with oral iron'. The significance level adopted will be 5%. The estimates will be made according to the 3 × 3 table for the results distribution from diagnostic accuracy phase III studies, which have cells to report unconcluded

results (lost, not performed or indeterminate) of the gold standard and the studied tests [23]. This table enables to report the results unknown that could bias the measurement of accuracy at a clinical practice setting (Table 1).

### Pilot study and interim analysis

During the period of the pilot study 106 anemic pregnant women were identified, which 39 fulfilled the eligibility criteria with the acceptance of 100% to participate in the research. The loss percentage was 41% due to dropout (9), gestational risk (5) and drug intolerance (2). Low therapeutic adherence (intake of less than 75% of pills) was observed in 30.4% (7/23) and the most incidents of adverse effects were nausea (25.8%), heartburn (21.5%) and constipation (17.2%).

An interim analysis of collected data will be performed on 186 pregnant women enrolled until August 2012, whose follow-ups were completed in November 2012, to verify the number of cases and non-cases and estimate the additional time necessary to achieve the sample size.

### Ethical issues

This protocol follows the Ethical Principles for Medical Research Involving Human Subjects of the Declaration of Helsinki and the 196/96 resolution from the National Health Council of Brazil. This study has the ethical approval for the human experimentation by IMIP Research Ethics Committee under the number 2050-10. The participants are duly informed about the research explained by the team and are enrolled in the study after having assigned the written informed consent form.

